### Randomization and Blinding

Randomization lists (1:1:1) were generated using a computer-based random number generator by an independent research assistant not involved in the project. Blocked randomization (with random block sizes of 3, 6, and 9) was used to ensure balanced group allocation. Given that randomization was stratified by gender (men, women, and other) and MSKD (low back pain, neck pain, rotator cuff-related shoulder pain, and anterior knee pain), 12 separate lists were generated. The randomization lists were integrated into the REDCap randomization module, eliminating the need for sealed envelopes. After the baseline evaluation, the research associate will enter the participant’s gender and MSKD type into REDCap, which will then generate the assigned group. The allocation will appear in a secure, concealed table within REDCap, preventing any modifications. The research associate will then inform the participant and the medical or physiotherapy clinic of the assigned group to schedule the participant’s first appointment.

Blinding of treatment providers and participants is not feasible due to the nature of the interventions. However, the statistician conducting the analyses will remain blinded to group allocation. Since all study outcomes are self-reported and collected via REDCap, an outcome assessor is not required. Participants will interact with a research associate only at baseline, before randomization. Participants will be informed that they are enrolled in 1 of 3 groups, that all groups receive high-value, individualized care, and that the number and frequency of follow-up sessions may vary. However, they will not be told whether they are assigned to a stepped care, usual rehabilitation care, or usual medical care, thereby maintaining partial blinding regarding group allocation. They will only be informed about the interventions received by participants in the other groups after completing the 24-week follow-up. To minimize potential contamination, each group will receive treatment in separate clinics: Usual medical care in medical clinics, while stepped care and usual rehabilitation care will be provided in different physiotherapy clinics. Co-interventions will be monitored at each follow-up using a questionnaire on REDCap.

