#### Anterior Knee Pain

Inclusion criteria are (1) anterior knee pain during walking, running or going up or down stairs, or during at least two activities among: kneeling, squatting, and resisted knee extension [55] and (2) maximum score of 79/100 on the Knee Outcome Survey Activities of Daily Living Scale (1.5 times the minimally clinically important difference [56], to ensure participants have clinically significant symptoms). Exclusion criteria are (1) history of knee surgery or patellar dislocation, and (2) pain believed to originate either from the meniscus [57] or any knee ligament based on clinical tests.

The primary objective is to assess the equivalence between the stepped care model and the 2 usual care models. With 123 participants per group, we will have 80% power to test the noninferiority of the stepped care model compared to usual rehabilitation care and usual medical care, using a noninferiority margin of 2.0 (out of 10) points on the primary outcome measure. This margin is based on the highest suggested minimally clinically important difference for the Pain Interference subscale of the Brief Pain Inventory—Short Form (BPI-SF) [58]. The sample size calculation assumes a true mean difference of 0 between groups, and an SD of 1.8 in the usual care groups [59], a 15% dropout rate at the 24-week follow-up [20,60-62], and a 1-sided alpha level of .025.

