### Training of Treatment Providers

Given the pragmatic nature of the interventions in the usual medical care and usual rehabilitation care groups, the physiotherapists and family physicians in these groups will not receive specific training related to the intervention. However, they will attend a 60-minute meeting outlining the study objectives and relevant procedures (eg, maximum number of consultations, the brief questionnaire to be completed in REDCap, and the expectation that they provide care according to their usual practices).

Physiotherapists delivering the educational intervention were selected based on their expertise in a clinic specializing in educational approaches for MSKDs. They will participate in a 2-hour in-person training session led by 3 members of the research team. This training will emphasize the educational components to be delivered and the importance of establishing a strong therapeutic alliance with participants. The study’s educational website will also be presented and explained during this session. To ensure consistency, follow-up meetings will be held twice a year to discuss strategies for maintaining standardization and to address any challenges that arise.

It should be noted that physiotherapists and family physicians providing usual medical care and usual rehabilitation care will not have access to the educational website, nor will it be presented to them.

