### Statistical Analysis Plan

Descriptive statistics will be used to summarize participants’ characteristics and outcome measures at the different measurement times. Participants who withdraw from the study and the reasons for withdrawal will be analyzed. Any harm or unintended effects will be recorded by both the treating family physician and physiotherapist at the beginning of each consultation, as well as by the participants during the follow-up evaluations on REDCap. If a participant experiences an adverse event, the principal investigator will report it to the Ethics Committee. However, since the interventions included in this trial are commonly used in clinical practice and are generally well tolerated, no major adverse events directly related to the intervention are expected, except perhaps a temporary increase in pain.

For each of the primary and secondary patient-reported outcome measures, repeated measures analyses will be performed using linear mixed models with a random effect by participant to account for the correlation present in repeated measures within individuals. The model allows assessment of the group and time effects, as well as the group-by-time interaction. An intention-to-treat analysis will be used. Gender and type of MSKD will be used to test the interaction between the group effect and the strata in order to test whether the comparison across interventions depends on gender or type of MSKD. Residual analysis will be performed to verify that the assumptions of normality and homoscedasticity are met. If not, the model will be extended to a generalized linear mixed-model framework. Effect sizes will be presented as the standardized differences between treatment groups in the mean weekly improvements over 12 and 24 weeks. Satisfaction will be compared using chi-squared tests, Mann-Whitney tests, or independent *t* tests.

For economic analyses, the total cost of an episode of care will be calculated from the perspectives of the public health service, the participants, and private insurers. ICERs will then be computed from 3 perspectives: the public health service, the participant, and society. The ICERs will be measured as the difference between the mean costs divided by the difference in effectiveness at 24 weeks between the stepped care model and each of the usual care models [95].

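### Clinics and clinicians are nested within arm, but the stated model has only a participant random effect; if outcomes correlate within clinician, the arm-difference intervals are too narrow

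*Protocol article*

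**What the plan says.** Participants are randomized individually, 1:1:1, stratified by gender and type of disorder. Clinic and clinician are not stratification factors. To limit contamination, "each group will receive treatment in separate clinics" (Protocol article, Randomization and Blinding), and the two physiotherapy-based arms also use different clinics from each other. Under Intervention, family physicians deliver usual medical care and physiotherapists deliver the other two arms. Under Training of Treatment Providers, "Physiotherapists delivering the educational intervention were selected based on their expertise in a clinic specializing in educational approaches for MSKDs"; they are trained separately, and usual-care clinicians are not shown the educational website.

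For every primary and secondary patient-reported outcome, the Statistical Analysis Plan section specifies "linear mixed models with a random effect by participant to account for the correlation present in repeated measures within individuals". It names no clinician or clinic term and no cluster-robust variance.

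The sample-size paragraph (end of Population and Sample Size, printed under Anterior Knee Pain) states: "With 123 participants per group, we will have 80% power to test the noninferiority of the stepped care model", "using a noninferiority margin of 2.0 (out of 10) points". The calculation "assumes a true mean difference of 0 between groups", and "an SD of 1.8 in the usual care groups". It lists no ICC or design effect.

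**The concern.** When the same clinicians treat patients in every arm, differences between clinicians largely cancel in the arm comparison. Here no clinician is described as working in more than one arm, so those differences go straight into the arm contrast. A model that treats participants as independent once their own repeated measures are handled leaves that variance out of the standard error.

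Some clinician variation is plausible on the article's own account. Clinicians with a deliberate range of experience are recruited, care is individualized in both usual-care arms, and Strengths and Limitations accepts that usual care will vary. In a noninferiority trial, an interval that is too narrow errs towards the hypothesis the trial hopes to support. The same model serves the secondary outcomes.

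**Working it through.** **1. The plan's own figure.** Inputs from the sample-size paragraph: margin 2.0, SD 1.8, true difference 0, one-sided alpha 0.025, power 80%, dropout 15%.

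n per arm = 2 × [SD × (z₀.₉₇₅ + z₀.₈₀) / margin]² = 2 × [1.8 × (1.960 + 0.842) / 2.0]² = 12.7, so 13 evaluable; 13 / 0.85 = 15.3, so 16 per arm.

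The stated 123 is not reproduced. That is a separate matter and nothing below depends on it; 123 is taken as the planned size.

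**2. Precision if participants are independent.** Evaluable per arm = 123 × 0.85 = 104.55. SE of a two-arm difference = 1.8 × √(2 / 104.55) = 0.249. The 95% half-width is 1.96 × 0.249 = 0.49 points. Any gain from baseline adjustment is ignored.

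**3. Effect of clustering on the error rate.** Participants per clinician (m) and the ICC are assumptions, taken as equal in both compared arms.

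- Design effect DE = 1 + (m − 1) × ICC
- True SE = 0.249 × √DE
- Actual one-sided error at the margin, using the unadjusted SE = Φ(−1.96 / √DE)

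| m (clinicians per arm = 104.55 / m) | ICC 0.01 | ICC 0.02 | ICC 0.05 |
|---|---|---|---|
| 10 (about 10.5) | DE 1.09, 3.0% | DE 1.18, 3.6% | DE 1.45, 5.2% |
| 20 (about 5.2) | DE 1.19, 3.6% | DE 1.38, 4.8% | DE 1.95, 8.0% |
| 40 (about 2.6) | DE 1.39, 4.8% | DE 1.78, 7.1% | DE 2.95, 12.7% |

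The margin does not enter the error formula, so a wide margin does not protect the error rate at the boundary.

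If only one arm is heavily clustered, the two design effects average. With m = 40 in one arm, m = 10 in the other and ICC 0.05, DE = (2.95 + 1.45) / 2 = 2.20, and the error is Φ(−1.96 / 1.483) = 9.3%.

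**4. Corrected interval width.** Half-width = t × 0.249 × √DE on 2(k − 1) degrees of freedom, for k clinicians per arm and m = 104.55 / k. At ICC 0.05 it runs from 0.55 points (k = 20) to 1.13 points (k = 3: 2.776 × 0.249 × 1.64), against 0.49 unadjusted.

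**5. Power at the stated margin.** By normal approximation, power = Φ(2.0 / (0.249 × √DE) − 1.96).

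- DE 1.38: Φ(6.84 − 1.96), above 99.99%.
- DE 2.95: Φ(4.68 − 1.96) = 99.7%.

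With a noncentral t on 2(k − 1) degrees of freedom, three clinicians per arm and ICC 0.05 give about 95%. Two clinicians per arm give 88%, 80% and 61% at ICC 0.01, 0.02 and 0.05.

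**The case against.** **The size is assumed.** With no ICC or clinician count in the article, the inflation cannot be computed, and at ICC 0 the stated intervals are right. The upper end needs about 2.6 clinicians in each of two arms, and nothing in the article supports that for family physicians spread over family medicine groups. This stands: the point is conditional, and 12.7% is the edge of an assumed range, not an estimate.

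**This may be left to a fuller plan.** The article is condensed, and naming a participant effect does not exclude others. That is fair, and a fuller document may add a clinician term. But the article does state the random-effect structure and its purpose, and that purpose covers only correlation within individuals. The point concerns what is written.

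**The margin is wide.** Even the corrected half-width of 1.13 is well inside 2.0, so a true difference near zero would normally still be declared noninferior. This also stands. It limits the practical effect on the primary conclusion, but not the error rate at the margin or the intervals for secondary outcomes.

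**A simple clinician intercept would not fit.** The primary measure is completed before randomization and so before any contact with a study clinician. If baseline is one of the repeated measures, a time-constant intercept would impose clinician correlation where none can exist, and it would cancel from change-from-baseline contrasts. This is correct and shapes the fix.

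**Two stronger readings are not supported.** A reader might infer that the stated power is overstated; step 5 shows otherwise at the article's own margin and SD, except with about two clinicians in an arm. A reader might also infer that stepped care is delivered by a few physiotherapists in one specialised clinic. The training section does refer to a clinic in the singular when describing how the education physiotherapists were chosen, but it gives no number, and the Intervention section places both physiotherapy-based arms in clinics, plural, across the city area.

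**Conclusion.** The point holds in conditional form. Clinics are nested within arm by explicit statement, clinicians by the roles described, and the stated model has no term for either. For any positive clinician ICC, the standard error of each arm difference is understated and the one-sided noninferiority error is above 2.5%. A moderate case (20 participants per clinician, ICC 0.02) gives 4.8%. All such figures rest on assumed cluster sizes and ICCs, equal-sized clusters and a normal approximation.

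No claim is made about power. Separately from the standard error, the design confounds each arm with the clinics that deliver it, and no analysis can undo that. This is a worthwhile and inexpensive correction, not a defect that invalidates the trial.

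**What to change.** In the Statistical Analysis Plan section:

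1. Add a random effect for treating clinician that applies to the post-baseline measurements only.
2. Define treating clinician as the first clinician to treat the participant after allocation. Stepped care may involve different physiotherapists for education and later rehabilitation, and usual-care participants may be referred elsewhere, so the definition must be fixed in advance.
3. Allow an arm-specific clinician variance where it can be estimated, use small-sample degrees of freedom, and report the ICC.
4. If there are too few clinicians to estimate the variance, repeat the primary interval for each comparison at fixed ICCs of 0.01, 0.02 and 0.05.
5. State as a limitation that arm effects cannot be separated from the effects of the clinics delivering them.

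The cost is wider intervals and fewer degrees of freedom; with three or four clinicians in an arm, the fixed-ICC analysis may be the only usable one. No new data collection should be needed, because clinicians in all three arms already complete a REDCap form after each session; it should be confirmed that the form identifies the clinician. By September 2025, 65 of 369 participants were enrolled and no interim analysis is planned, so the change can be made before any arm comparison is seen.

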### Intervention

Usual medical care will be provided by family physicians practicing in family medicine groups or university-affiliated family medicine groups, while usual rehabilitation care and stepped care will be provided by physiotherapists practicing in physiotherapy clinics across the Quebec City area. To enhance the generalizability of findings to the broader health care workforce, family physicians and physiotherapists with varying levels of experience, from early-career to experienced clinicians, will be included. Each intervention will have a maximum duration of 12 weeks. All consultation fees with the family physicians and physiotherapists related to the study will be covered by the research team.

### Stepped Care Group

During the first 6 weeks, participants in the stepped care group will engage in a web-based self-management education program, supplemented by 2 individual educational sessions with a physiotherapist. The first session (60 minutes) will begin with a clinical evaluation by the physiotherapist responsible for the educational intervention, followed by an education session covering the anatomy, function, and diagnosis of the affected area, basics of pain neuroscience, and condition-specific guidance on load management [27]. Participants will also receive strategies for pain and activity (pacing) self-management, optimal sleep and work positions, and key lifestyle factors such as stress management and nutrition [19,63]. The importance of physical activity will be emphasized, with recommendations aligned with World Health Organization guidelines (ie, 150-300 minutes of moderate-intensity activity per week), and adapted to each participant’s condition and physical capacity. Throughout the session, physiotherapists will foster open dialogue, personalizing discussions to address each participant’s needs and goals, answering questions, dispelling myths or misconceptions, providing reassurance, and discussing prognosis. An educational website, developed in collaboration with 7 patient partners, will also be introduced. It offers additional resources, including educational videos, summaries of key topics, and supplementary material for reference. Participants will be encouraged to explore these resources independently during the following weeks. The research team will have access to data on time spent on the website throughout the study.

The second educational session (30 minutes), scheduled 2 to 4 weeks later, will focus on reinforcing key concepts and providing long-term recommendations. The physiotherapist will begin by reviewing the participant’s condition and assessing their understanding of the material from the first session and the website. They will verify whether the participant has engaged with the educational website’s online content, address any remaining questions, offer personalized guidance, and provide recommendations for long-term self-management. While the second educational session will be preferably conducted in person, it may also be held via telehealth, depending on the participant’s preference. Following each session, the physiotherapist will complete a brief REDCap questionnaire documenting the topics discussed.

At the 6-week follow-up evaluation, participants in the stepped care group will be assessed using a region-specific patient-reported outcome measure to determine if their condition has resolved. Participants who no longer experience clinically important symptoms at the 6-week follow-up will be classified as “resolved” and will not receive further intervention. Those with scores exceeding the minimal clinically important difference thresholds on their region-specific patient-reported outcome measure (low back pain >10 on the ODI; neck pain >14 on the Neck Disability Index [NDI]; rotator cuff-related shoulder pain >10 on the QuickDASH; and anterior knee pain <86 on the Knee Outcome Survey Activities of Daily Living Scale [KOS-ADLS]) will be considered “unresolved” and will receive follow-up rehabilitation interventions. This dichotomization approach between “resolved” and “unresolved” MSKDs was chosen because, while an improvement greater than the minimal clinically important difference would be indicative of clinically significant improvement, participants may still experience substantial symptoms and limitations if their total score remains above the minimal clinically important difference threshold [64]. Participants classified as “unresolved” will undergo a rehabilitation intervention supervised by a physiotherapist over the following 6 weeks. This intervention will mirror the usual rehabilitation care group’s approach but will be condensed into a maximum of 5 sessions within a 6-week period. To prevent bias in patient-reported outcome measures responses, participants will not be informed during the first 6 weeks that they may be eligible for additional physiotherapy sessions if their symptoms remain clinically significant at the 6-week follow-up. Similarly, participants classified as “resolved” will not be informed at the 6-week mark that additional treatments could have been offered if their symptoms had persisted after the educational intervention. This information will only be disclosed at the end of the study, at the 24-week follow-up.

### Usual Rehabilitation Care Group

Participants will engage in a pragmatic 12-week rehabilitation intervention led by a physiotherapist, consisting of up to 10 individualized sessions, each lasting 30 minutes (except for the initial 60-minute session), along with an individualized home exercise program. During the first session, the physiotherapist will conduct an initial clinical evaluation. Given the pragmatic nature of the intervention, its structure and modalities will remain flexible, shaped collaboratively by the physiotherapist and the participant. This approach will take into account the participant’s goals and preferences, as well as the observed disabilities and the severity of the condition. Exercises may be used to improve strength, endurance, flexibility, the ability to sustain mechanical load, and dynamic control, as needed. In addition, participants may receive educational information related to their painful area, along with advice on pain and load management, activity modification, and any other relevant topics as determined by the treating physiotherapist. Manual therapy techniques (eg, massage, mobilization, or manipulation) and other passive interventions (eg, electrotherapy, heat, ice, dry needling, or any type of taping) may be used during sessions based on pragmatic clinical decision-making [65]. At the end of each supervised session, participants may receive individualized exercises, with progression, to perform at home between sessions.

If participants become symptom-free before completing the 10 sessions, or if the participant and physiotherapist determine that no further sessions are needed, treatment will be discontinued. Participants will then receive advice, recommendations, and home exercises as appropriate. If needed, they will have the option to resume the intervention within the 12-week period. Participants will not be restrained from using over-the-counter medications for pain relief if deemed helpful. If pain persists, the physiotherapist may refer participants to a family physician for further medical evaluation and management, which may include diagnostic tests (clinical, laboratory, or imaging), pharmacological pain management, and corticosteroid injections. Participants may also be referred to other health care providers (eg, psychologists, occupational therapists, and kinesiologists). However, these referrals will not be managed by the research team, and the associated costs will be the participant's responsibility. After each supervised session, the physiotherapist will complete a short REDCap questionnaire detailing the intervention modalities used, exercises prescribed, any referrals made, and the follow-up plan.

